### Sample size calculation and statistical analyses

Sample size and power analysis: For the three primary objectives the following analyses are used: a) a superiority analysis for the reduction in the percentage of febrile patients receiving antibiotics. b) a noninferiority analysis for safety, and c) an analysis of the test characteristics (sensitivity and specificity) of the biomarker PCT and CRP. The total sample size calculation is based on a power analysis for each of these three primary outcome measures; the total sample size is the maximum of the required sample sizes for the different primary outcome measures.For the superiority analysis of the reduction in the prescription of antibiotics, we assumed that antibiotics are initially prescribed at the ED to 73 % of the patients in the control arm, and that the intervention will reduce this percentage to 53 %, based on a careful estimate using recent literature [14]. To obtain 80 % power to detect a significant difference between the two groups using a two-sided Fisher’s exact test with a significance level of 5 %, the required sample size is 101 patients per group.The noninferiority analysis for the safety objective uses a composite endpoint consisting of ICU admittance, 30-days mortality or second ED visit within 14 days. For an accurate sample size calculation, we first analyzed ED data from the Erasmus MC from January 2011 until May 2012. In this data set, the prevalence of the composite safety endpoint was 12.7 % (102 cases out of 809 patients). We used this percentage as the expected rate in the control group. Using a noninferiority margin of 7.5 %, a noninferiority analysis comparing the rates in the control and the intervention groups requires 244 patients in each group to obtain 80 % power with a one-sided alpha of 5 %. To account for 10 % expected dropout, the total sample size must be 550 patients.The third sample size calculation is based on a comparison of sensitivity and specificity of PCT and CRP in patients with infection. We used data from a meta-analysis [21, 22] to estimate the accuracy of PCT and CRP for bacterial infection. We conservatively assumed zero correlation between the test results of PCT and CRP for the diagnosis of bacterial infection. For the prevalence of bacterial infections, we used data from our pilot study [3] to obtain a representative estimate of the prevalence of bacterial infections, which led to an estimated prevalence of 68 %. Based on the results of the meta-analysis, the sensitivity of PCT was 0.83 and for CRP 0.73; the specificity was 0.88 for PCT and 0.60 for CRP. Using McNemar’s test, 340 patients with a bacterial infection (340/0.68 = 500 patients in total) are required to obtain 80 % power for detecting a difference in sensitivity between PCT and CRP. Forty-one patients without a bacterial infection (41/(1–0.68) = 129 patients in total) are required to obtain 80 % power for detecting a difference in specificity between PCT and CRP. To ensure sufficient power for all three primary outcome measures, we thus use a sample size of 275 patients per group (550 patients in total).

Statistical analyses for the primary study parameters:Antibiotics use. The percentage of patients that are prescribed antibiotics is compared between the PCT-guided group and control group using a Fisher’s exact test. Demographic parameters (age, sex, mortality), medical parameters (medication use, comorbidity, temperature, CRP and PCT measurements), hospital admission related parameters (hospital admittance, hospital length of stay, ICU admittance, ICU length of stay) are compared between the PCT-guided group and control group using Fisher’s exact tests for dichotomous variables, chi-square tests for categorical variables with more than two categories, t-tests for continuous variables that are normally distributed, and Kruskal-Wallis tests for continuous variables that are not normally distributed. A logistic regression analysis will be used to determine the influence of these parameters on the proportion of antibiotics prescriptions in the control group and the PCT-guided therapy group. To select the independent variables in this logistic regression model, we will use a stepwise backward approach in which only the independent variables are retained that have a significant effect using a significance level of 5 %; however, the variable group (PCT-guided group versus control group) will be included in the model irrespective of the results. In the event of missing values in possible confounding data, like intoxications and prescription drugs use, we will use multiple imputation. Both an intention to treat analysis and a per protocol analysis will be performed. Physician adherence to the PCT guidance will be determined.Safety. Significant differences between the PCT-guided group and control group in the composite safety endpoint are determined using a one-sided upper 95 % confidence limit for the difference in proportion between the PCT-guided group and the control group. This confidence interval will be calculated using the method of Agresti and Caffo [23]. Noninferiority of the intervention will be established if the 95 % confidence interval excludes 7.5 %, i.e. if PCT-guided prescription of antibiotics does not increase the rate of the composite endpoint by more than 7.5 percentage points. Differences in hospital length of stay will be assessed using the Kruskal-Wallis test.Accuracy of PCT and CRP. In all patients, the final diagnosis of the etiology of fever will be determined. Also, it will be determined if there is a bacterial infection. The variables “confirmed bacterial infection” and “suspected bacterial infection” will serve as gold standards for the evaluation of the accuracy of the biomarkers CRP and PCT. These will be determined retrospectively, using culture results and all diagnostic tests available. In all patients, both PCT and CRP levels will be available for statistical analysis. The ability to predict bacterial infection of both PCT and CRP will be evaluated using receiver operating characteristic curves, and the area under the curve will be calculated. In addition, logistic regression will be performed to analyze the effects of PCT and CRP levels on the probability of a bacterial infection. The independent variables in this analysis are age, sex, PCT, CRP, temperature, comorbidity, and other variables that have a *p* < 0.1 for the difference between groups. We will account for possible non-linear effects of age, PCT, CRP and temperature by using appropriate transformations of these variables.

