**Methods/design:**

This is a multicenter noninferiority randomized controlled trial. All adult ED patients with fever(≥38.2 °C) are randomized between standard care with and without the addition of a PCT level, after written informed consent.For efficacy, the reduction of patients receiving antibiotics is calculated, using a superiority analysis: differences between the PCT-guided group and control group are assessed using a Fisher’s exact test, and a multivariable logistic regression analysis to account for the effects of demographic and medical variables on the percentage of febrile patients receiving antibiotics.Safety consists of a composite endpoint, defined as mortality, intensive care admission and ED return visit within 14 days. Noninferiority of PCT will be tested using a one-sided 95 % confidence interval for the difference in the composite safety endpoint between the PCT-guided and control groups using a noninferiority margin of 7.5 %.Accuracy of PCT and CRP for the diagnosis of bacterial infections will be reported, using the sensitivity, specificity, and the area under the receiver-operating-characteristic curve in the definitive diagnosis of bacterial infections.

The sample size is 550 patients, which was calculated using a power analysis for all primary objectives. Enrollment of patients started in August 2014 and will last 2 years.

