### Outcome measures

#### Primary outcome measures

The efficacy of PCT-guided therapy is defined as the percentage of patients who are prescribed antibiotics in the ED.The safety outcome measure consists of a composite endpoint of 30 days mortality, intensive care unit (ICU) admission within 30 days, or a return visit to the ED within 14 days.The accuracy of the definitive diagnosis is reported for PCT and CRP using the sensitivity, specificity, and the AUC of the diagnosis of bacterial infections. The definitive diagnosis is defined in two ways. 1. As “confirmed bacterial infection”, in which culture – and PCR results that fit the clinical case presentation are used to report presence of bacterial infections. 2. As “suspected bacterial infection”, in which two independent physicians will give their expert opinion on the presence of a bacterial infection using culture results, image modalities and clinical course, in case of discrepancy, a third physician will decide.

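### The adjusted efficacy model admits post-randomisation variables (mortality, admission, ICU admission, length of stay) as candidate covariates, which puts its PCT-group odds ratio at risk of bias

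*Protocol article*

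**What the plan says.** The Protocol article, under Primary outcome measures, sets the efficacy outcome: "The efficacy of PCT-guided therapy is defined as the percentage of patients who are prescribed antibiotics in the ED".

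The text on antibiotics use, under Sample size calculation and statistical analyses, starts with a Fisher's exact test between the groups. It then lists three families of variables to be compared by group:

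- The first family, which counts death as a demographic item, reads "Demographic parameters (age, sex, mortality").
- The second family is clinical: drugs taken, comorbid disease, body temperature and the two biomarkers.
- The third family concerns the hospital stay and reads "hospital admission related parameters (hospital admittance, hospital length of stay, ICU admittance, ICU length of stay").

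The same list is carried into a model: "A logistic regression analysis will be used to determine the influence of these parameters on the proportion of antibiotics prescriptions", separately naming the control and PCT-guided groups. On selection it says "we will use a stepwise backward approach in which only the independent variables are retained that have a significant effect", at the 5% level, but "the variable group (PCT-guided group versus control group) will be included in the model irrespective of the results".

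The abstract (Methods/design) places this regression next to Fisher's test in the superiority analysis, as "a multivariable logistic regression analysis to account for the effects of demographic and medical variables".

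**The concern.** A covariate in an adjusted treatment comparison should be fixed before the treatment can act on it. Five of the listed candidates do not meet that condition. Death and length of stay in hospital or ICU are known only after the ED prescription has been written, so they cannot have influenced it. Hospital and ICU admission are settled after randomisation, at a time when the PCT result may be on the clinician's screen in one arm. Death within 30 days and ICU admission within 30 days are also components of the trial's own safety endpoint.

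Because group stays in the model whatever happens, the output includes an adjusted PCT effect. If an admission variable survives selection, that effect is conditional on something that both the arm and the prescription may have changed. At stake is whether the adjusted odds ratio reported beside the primary efficacy test estimates the effect of PCT guidance on prescribing.

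**Working it through.** **1. The plan's own efficacy figure.** Inputs from the sample size section: 73% against 53%, two-sided 5%, 80% power, Fisher's exact test. The continuity-corrected two-proportion formula gives 101 per group (91 without the correction). Exact enumeration of Fisher's test gives power of 80.6% at 101 and 79.96% at 100. The stated 101 per group is reproduced, and power at 275 per group is 99.8%. None of this involves the regression.

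The design odds ratio is (0.53/0.47) / (0.73/0.27) = 1.1277/2.7037 = 0.417.

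**2. Timing of the candidates.**

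| Candidate | Position relative to the ED prescription |
|---|---|
| age, sex, comorbidity, triage temperature | before |
| CRP | blood drawn at inclusion |
| hospital admission, ICU admission | after randomisation; order relative to prescribing not stated |
| hospital and ICU length of stay, mortality | after |

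No sentence in the article limits the candidates to baseline variables.

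**3. What conditioning on admission does.** The documents give no effect sizes, so the following are assumptions. Let the log-odds of admission be -0.5 + a (if antibiotics) + d (if PCT group), and let P(y,g) be the resulting probability with antibiotics y in group g. By Bayes' rule, the group odds ratio for antibiotics given admission status is

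OR x K, with K = P(1,1) P(0,0) / [P(1,0) P(0,1)].

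There is no interaction in this admission model, so K is the same among admitted and non-admitted patients.

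- a = 1, d = -0.5: K = (0.5000 x 0.3775)/(0.6225 x 0.2689) = 1.128
- a = 2, d = -0.5: K = (0.7311 x 0.3775)/(0.8176 x 0.2689) = 1.255
- a = 2, d = -1.0: K = (0.6225 x 0.3775)/(0.8176 x 0.1824) = 1.576
- a = 2, d = 0: K = 1

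**4. Simulation at the planned size.** 275 per arm, 1,500 trials per row, admission kept if p < 0.05. It was kept in 100% of trials in every row.

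| True OR | a | d | OR x K | Simulated OR after selection | Rejection: group only, then after selection |
|---|---|---|---|---|---|
| 0.417 | 1 | -0.5 | 0.470 | 0.468 | 99.9%, 98.5% |
| 0.417 | 2 | -0.5 | 0.524 | 0.522 | 99.9%, 88.3% |
| 1 | 2 | -0.5 | 1.255 | 1.26 | 5.3%, 18.1% |
| 1 | 2 | -1.0 | 1.576 | 1.59 | 5.3%, 56.5% |
| 1 | 2 | 0 | 1.000 | 1.00 | 5.3%, 4.7% |

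The model with group alone gave 0.415 for the design value 0.417.

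**5. A shared cause.** In samples of 400,000, let severity raise the log-odds of both prescribing and admission by 0.8 per SD, with a = 2 and d = 0. The group odds ratio is 0.462 with neither covariate, 0.418 with severity, and 0.439 with admission in place of severity. The last value matches neither of the others. Part of such shifts is the non-collapsibility of the odds ratio: with a = 0, adding admission still moves 0.462 to 0.457. With severity in the model and d = -0.5, adding admission and length of stay still moves 0.418 to 0.517, so good baseline adjustment does not remove the problem.

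**The case against.** The strongest reply is that the trial's efficacy inference does not depend on this model. Efficacy is powered on an unadjusted Fisher's exact test, which opens the efficacy analysis and uses no covariates. That stands. A reader might infer that the randomised comparison is destroyed, but the documents do not support this: only the adjusted estimate is exposed.

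The second reply is that bias is not certain. It needs a route from arm to the later variable that bypasses antibiotics, or an unmodelled shared cause. That also stands, as the last row of the table shows. The Background makes a direct route plausible, since it suggests that PCT guidance may make admission for observation unnecessary, but it gives no size.

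Some further inferences should not be drawn:

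- That every listed event follows the prescription. The order of the admission decision and the prescription within the ED visit is undocumented; only length of stay and mortality are later by their nature.
- That PCT level enters as a main effect only. The article does not say so, and its sentence names both groups, which leaves room for arm-specific influence.
- That backward selection makes the group interval too narrow. In one simulation with group forced in (550 patients, eight baseline covariates, 3,000 trials), coverage was 95.1% under no effect and 95.0% with a group log-odds of -1.0. That is one set of assumed covariates and no general proof, but material narrowing has not been shown.
- That the abstract contradicts the methods. It is a condensed summary, and the methods file mortality under demographic variables. Only the admission family goes unmentioned.

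None of this answers the core point. The article positively names these variables as candidates, so it is not a detail left to an analysis plan.

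**Conclusion.** The point holds for the adjusted efficacy model only. As written, five post-randomisation variables are eligible for it, and one that is strongly related to prescribing, as admission was in the simulations, will survive selection. The adjusted PCT-group odds ratio is then at risk of bias.

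Size and direction are not derivable from the documents. Under the assumed effects above, the odds ratio moves from about 0.42 to between 0.47 and 0.52, or from 1.00 to between 1.26 and 1.59. The first shift is toward no effect and the second away from it, so a reader should not conclude that the bias is always conservative. With no direct effect of PCT guidance on admission and no shared cause, there is no shift.

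Fisher's exact test, the safety analysis and the figure of 101 per group are unaffected. The model should be corrected because it is presented beside a primary comparison, but the defect does not endanger the trial's main efficacy test.

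**What to change.** State that the candidate covariates of the adjusted efficacy model are pre-specified and limited to variables measured before the PCT result and the antibiotic decision: for example study site, age, sex, comorbidity, medication at baseline, temperature and CRP, with group always included. Remove mortality, hospital admission, ICU admission and both lengths of stay from the candidates, and report them only as outcomes by group. Align the abstract's description with the revised list.

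The cost is wording in the analysis section. No new data or patients are needed, and no stated sample size changes.

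### Backward elimination at 5 % distorts the reported influence of weak covariates on antibiotic prescribing, but leaves the treatment comparison essentially intact

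*Protocol article*

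**What the plan says.** Under Sample size calculation and statistical analyses, the item on antibiotics use compares the two groups with an unadjusted Fisher's exact test. It then lists demographic, medical and admission-related parameters and adds a model: "A logistic regression analysis will be used to determine the influence of these parameters on the proportion of antibiotics prescriptions" in the two groups. Its terms are chosen by "a stepwise backward approach in which only the independent variables are retained that have a significant effect", at a 5 % level. Only treatment is exempt: "the variable group (PCT-guided group versus control group) will be included in the model irrespective of the results".

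The article states no shrinkage, no resampling of the selection, no report of the full model and no interval for these coefficients. The Abstract describes the same regression differently, as a way to account for demographic and medical variables in the efficacy comparison.

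**The concern.** Determining the influence of a parameter is an estimation task. Elimination filters the estimates by significance in the same data. A weak but real determinant passes the filter mainly when chance has pushed its estimate away from no effect, so the surviving estimates are biased outward. A model-based interval computed after selection ignores that step. The set of adjustment variables is also chosen by the data and not fixed in advance. What is at stake is the account of what drives prescribing, not whether PCT guidance reduces it.

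**Working it through.** **Inputs from the article.** Control prescribing is assumed to be 73 %, and "the intervention will reduce this percentage to 53" %. There are 275 patients per group (550 in total) and 10 % dropout. Retention is at 5 % with group forced in. There are 3 demographic + 5 medical + 4 admission parameters = 12 candidates.

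**Assumptions, because the article gives none.** Two-sided Wald tests, standardised covariates, and the true odds ratios (OR) and correlations shown below.

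**1. The plan's own figure.** For 73 % v 53 %, two-sided 5 %, 80 % power, the mean proportion is 0.63. Without continuity correction, n = [1.96·√(2·0.63·0.37) + 0.842·√(0.73·0.27 + 0.53·0.47)]² / 0.20² ≈ 90.3, or 91. With the correction it is 101 per group, as stated. Exact Fisher power at 101 is 0.806.

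**2. Where the filter bites.** The standard error of a log OR per SD is at least 1/√(550·0.63·0.37) = 0.088, so the retention threshold is at least 1.96·0.088 = 0.173 (OR 1.19). In the adjusted model the standard error is about 0.10 (simulated mean 0.101 at zero correlation), giving a threshold of 0.196 (OR 1.22). A true OR of 1.2 sits almost on it.

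**3. Closed-form check for OR 1.2.** θ = ln 1.2 = 0.182 and SE = 0.10, so a = 1.96 − 0.182/0.10 ≈ 0.14. P(kept) = 1 − Φ(0.14) ≈ 0.45. The mean when kept is 0.182 + 0.10·φ(0.14)/0.45 ≈ 0.271, which is 1.49 times the truth.

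**4. Simulation with a comparator.** 550 patients, 2000 trials, ten candidates (two OR 1.8, three OR 1.2, five null). Elimination is set against the full model read only where p < 0.05.

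| | Elimination, corr. 0 | Full, p < 0.05, corr. 0 | Elimination, corr. 0.3 | Full, p < 0.05, corr. 0.3 |
|---|---|---|---|---|
| OR 1.2 dropped or non-significant | 54 % | 54 % | 59 % | 66.5 % |
| Log OR when kept / truth | 1.49 | 1.51 | 1.73 | 1.75 |
| 95 % interval coverage when kept | 95 % | 94 % | 91 % | 92 % |
| At least one null kept | 24 % | 24 % | 27 % | 22 % |

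Repeat runs moved the last row to 23 % v 23 % (correlation 0) and up to 30 % v 24 % (correlation 0.3), and the coverage after elimination at correlation 0.3 to 89 %. Reading every term of the full model whatever its p-value gave 1.02 to 1.04 times the truth and 95 % coverage for OR 1.2. Group-effect coverage was 94 to 95 % either way.

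**5. Range of effect sizes.** Elimination, 12 candidates (four null), 1500 trials, correlation 0 / 0.3.

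| True OR per SD | Kept | Log OR when kept / truth | Coverage when kept |
|---|---|---|---|
| 1.1 | 17 % / 20 % | 2.55 / 3.17 | 81 % / 71 % |
| 1.2 | 46 % / 44 % | 1.49 / 1.80 | 94 % / 87 % |
| 1.3 | 77 % / 69 % | 1.17 / 1.38 | 97 % / 92 % |
| 1.5 | 98 % / 95 % | 1.03 / 1.14 | 96 % / 93 % |
| 2.0 | 100 % / 100 % | 1.01 / 1.07 | 94 % / 92 % |

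The full model with every term reported gave 1.02 to 1.06 times the truth and 94 to 95 % coverage throughout. The group log OR was −0.874 in truth and −0.877 / −0.889 on average after elimination, with coverage 94 % / 96 %.

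**6. Can the data carry a fixed model?** Patients without antibiotics: 0.27·275 + 0.47·275 = 74.25 + 129.25, about 203; after 10 % dropout about 183. Group plus six baseline covariates is seven terms if each needs one: 183/7 ≈ 26 per term. If comorbidity and medication use need several terms and the total reaches 13, 183/13 ≈ 14. At 495 patients with 13 terms, the simulated full model still covered at 94 to 95 %.

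**The case against.** The strongest reply is that this is an adjusted treatment comparison and not a study of determinants. The Abstract gives adjustment as the purpose, the covariates are called possible confounders, group is forced in, and no stated objective or outcome concerns what drives prescribing. That stands as a limit on scope, but the methods text does also assign the model the task of determining influence.

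The second reply is that most of the harm is ordinary significance filtering. This largely stands. Step 4 shows the same overstatement, and similar false-positive rates, when a full model is read only where p < 0.05. At correlation 0.3 the full model even misses more weak terms. Elimination itself adds about 5 to 6 points of null variables kept and costs 1 to 3 points of coverage, and only under correlation. A full model therefore helps only if every coefficient is reported and read.

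Third, the article names no interval for these terms, and reporting detail may sit in an analysis plan that is not shown. The statement on intervals is therefore conditional.

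A reader might infer that the efficacy result is biased, or that every retained effect is exaggerated with too narrow an interval. The documents do not support either. Fisher's test involves no selection, the forced group coefficient is stable, strong determinants barely move, and coverage at OR 1.2 is near nominal when candidates are uncorrelated.

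**Conclusion.** The point holds in a limited form, at minor to moderate severity. The stated rule biases the covariate estimates that the model is asked to deliver. A determinant with OR about 1.2 per SD is dropped in just over half of trials and, when kept, overstated about 1.5 to 1.7-fold (1.8-fold in the second scenario). If ordinary model-based intervals are reported, they cover it about 94 % of the time with uncorrelated candidates and about 90 % at correlation 0.3. Weaker effects fare worse; at OR 1.5 or more the inflation is at most about 14 %. All effect sizes and correlations are assumed. No efficacy, safety or accuracy conclusion depends on this.

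**What to change.** Replace the elimination sentence with one model fixed in advance. It contains group and the baseline covariates already listed (age, sex, comorbidity, medication use, temperature, CRP) and keeps every term whatever its p-value. Report all coefficients with 95 % intervals, and do not single out the significant ones as the determinants, since that would bring the filter back.

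The cost is one sentence, a few non-significant rows and slightly wider intervals; no patients or data are needed. Whether PCT and the variables that arise after the prescribing decision (mortality, admission, length of stay, ICU) belong in the model is a separate issue that dropping the elimination does not settle.

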## Background

Fever is one of the most common symptoms of patients visiting the emergency department (ED). The etiology of fever is diverse, ranging from infectious diseases to neoplasms and trauma [1]. Specific etiologies of fever, such as severe bacterial infections, have to be treated within one hour after ED presentation with adequate antibiotic therapy, according to the surviving sepsis guidelines [2].

Because time is of the essence in the initiation of therapy, physicians in the ED have a limited time window for diagnosing the etiology of fever. This results in a “better safe than sorry” approach, in which broad-spectrum antibiotics are administered to febrile patients, only based on history and physical examination, and readily available diagnostic entities.

On the other hand, antibiotic resistance is becoming an increasing problem worldwide. Antimicrobial stewardship advocates thoughtful initiation of antibiotic therapy. Thus, in treatment of bacterial infections, both under-treatment and overtreatment are undesirable. Therefore, it is vital to increase the accuracy of diagnostics of febrile illness.

The mainstay of diagnosing the etiology of fever in the ED consists of history, physical examination and laboratory analysis of serum and other bodily fluids, and chest X-ray examinations. Cultures and viral throat swabs are obtained, but are of no use in the ED, because results take several hours to days and treatment has to be started early after ED presentation [2]. Currently, leukocyte count, with or without leukocyte differentiation, and C-reactive protein (CRP) are the laboratory discriminators of choice in the initial approach in the diagnostic process of febrile diseases.

A higher accuracy of ruling in or ruling out bacterial infections using biomarkers may result in more accurate antimicrobial therapy. On the individual patient level, fewer patients would be treated empirically with antibiotics. Adverse events and drug interactions would be reduced. Also, a more accurate diagnosis could save hospital expenses and result in cost reductions. On a population level, antibiotics resistance could be countered. For patient safety, this should obviously be without an added risk of under-treatment.

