## Methods and design

The HiTEMP study is designed as a multicenter noninferiority randomized controlled trial on PCT-guided therapy. The study will be performed in both academic and non-academic teaching hospital settings. Patients will be asked for written informed consent. Patients who consent are randomized using an online computer program, to either the standard-of-care diagnostic workup of febrile patients (control group), or the standard-of-care workup with the addition of the diagnostic biomarker PCT.

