### Secondary outcome measures

Secondary outcome measures for cost-effectiveness are hospital treatment costs, related medical consumption during follow-up, costs of absenteeism and reduced productivity while at work.

The adherence to PCT advice is reported, including the percentage of antibiotic prescriptions with low PCT result, and withholding of antibiotics in patients with high PCT result.

The percentage of patients who received antibiotics without suspected bacterial infection is reported.

Outcome measures are reported for the total patient population, and are stratified by source of infection: respiratory tract infections, urinary tract infections, skin and soft tissue infections, central nervous system infections, abdominal infections, non-infectious fever, fever without source, and other causes of fever.

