### Laboratory examinations

Blood samples will be obtained at inclusion. Samples will be centrifuged (3000 N Relative centrifugal force (Rcf) at room temperature for 5 min). The serum will be measured on the routine analyzer of the clinical chemistry laboratory (Roche Cobas 8000 system, Roche Diagnostics Netherlands). PCT-measurements will be performed by using an electro-chemiluminiscent immunoassay (ECLIA) (Roche diagnostics, Brahms, Henningsdorf, Germany). All samples will be measured and reported without knowledge of the clinical status of the subjects.

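### The protocol article gives two different lists of evidence for the reference diagnosis, and the wider one admits CRP and PCT, the tests being evaluated

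*Protocol article*

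**What the plan says.** Accuracy of PCT for bacterial infection is one of three primary objectives, and a PCT-versus-CRP comparison of sensitivity and specificity is one of the three sample size calculations.

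The protocol article describes the reference diagnosis twice:

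- **Primary outcome measures.** For *confirmed* infection, culture results and "PCR results that fit the clinical case presentation are used to report presence of bacterial infections". For *suspected* infection, "two independent physicians will give their expert opinion on the presence of a bacterial infection using culture results, image modalities and clinical course", with a third physician if they disagree. Neither list names CRP or PCT.
- **Sample size calculation and statistical analyses.** Both variables are the gold standards for CRP and PCT, and "These will be determined retrospectively, using culture results and all diagnostic tests available". Nothing is excluded.

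The only masking statement is under Laboratory examinations: "All samples will be measured and reported without knowledge of the clinical status of the subjects". Secondary outcome measures adds a measure that depends on the panel's label: "The percentage of patients who received antibiotics without suspected bacterial infection is reported".

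**The concern.** A reference diagnosis should be set without the tests that it is used to judge. If adjudicators may consult CRP or PCT, some labels will agree with the marker because the marker shaped them. That is incorporation bias, and a larger sample does not remove it. The reference label is shared by both markers, so a label pulled towards one marker flatters that marker and can penalise the other. The comparison between them is therefore at risk, as well as each absolute value.

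The *suspected* standard is the more exposed, because it rests on opinion. If PCT were visible to the panel in one arm only, the share of patients given antibiotics without suspected infection would also be labelled differently by arm.

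**Working it through.** **1. The two descriptions side by side**

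| Standard | Primary outcome measures | Statistics section |
|---|---|---|
| Confirmed | Culture and PCR results that fit the presentation | Cultures plus every available diagnostic test |
| Suspected | Cultures, imaging, clinical course | The same sentence covers both standards |

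The second description is wider than the first, and the article does not say which governs.

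**2. Do CRP and PCT count as diagnostic tests here?** The article treats both as such. In Background, leukocyte count and "C-reactive protein (CRP) are the laboratory discriminators of choice in the initial approach in the diagnostic process of febrile diseases". In Methods and design, the intervention is "the standard-of-care workup with the addition of the diagnostic biomarker PCT". CRP therefore falls within the wider wording in both arms, and PCT at least in the PCT-guided arm.

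**3. Does the masking statement help?** It keeps the laboratory unaware of clinical status. The reverse protection, keeping adjudicators unaware of the marker results, is not stated.

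**4. How far could the comparison move?** The article gives no figure for this, so what follows is an illustration.

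Inputs from the sample size section: prevalence 0.68; PCT sensitivity 0.83 and specificity 0.88; CRP sensitivity 0.73 and specificity 0.60; zero correlation, taken here as independence given true status. Assumed: a share f_P of reference labels copies the PCT class, a share f_C copies the CRP class, and the remaining labels equal true status.

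- P(PCT+) = 0.68×0.83 + 0.32×0.12 = 0.5644 + 0.0384 = 0.6028
- P(CRP+) = 0.68×0.73 + 0.32×0.40 = 0.4964 + 0.1280 = 0.6244
- P(both+) = 0.68×0.83×0.73 + 0.32×0.12×0.40 = 0.4120 + 0.0154 = 0.4274
- P(label+) = (1−f_P−f_C)×0.68 + f_P×0.6028 + f_C×0.6244
- PCT sensitivity = [(1−f_P−f_C)×0.5644 + f_P×0.6028 + f_C×0.4274] / P(label+)
- CRP sensitivity = [(1−f_P−f_C)×0.4964 + f_P×0.4274 + f_C×0.6244] / P(label+)

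With no copying the formulas return the planning values: 0.5644/0.68 = 0.83 and 0.4964/0.68 = 0.73.

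With 10% copying CRP only:

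- P(label+) = 0.6120 + 0.0624 = 0.6744
- PCT: (0.5080 + 0.0427)/0.6744 = 0.817
- CRP: (0.4468 + 0.0624)/0.6744 = 0.755
- Gap: 0.062

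Specificity follows in the same way from the negative cells.

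| Labels copying | PCT sens. | CRP sens. | Gap | PCT spec. | CRP spec. |
|---|---|---|---|---|---|
| None | 0.830 | 0.730 | 0.100 | 0.880 | 0.600 |
| 5% each marker | 0.831 | 0.742 | 0.089 | 0.867 | 0.617 |
| 10% each marker | 0.832 | 0.753 | 0.078 | 0.855 | 0.634 |
| 20% each marker | 0.834 | 0.778 | 0.056 | 0.832 | 0.665 |
| 10% CRP only | 0.817 | 0.755 | 0.062 | 0.840 | 0.646 |
| 20% CRP only | 0.803 | 0.780 | 0.022 | 0.801 | 0.691 |
| 10% PCT only | 0.845 | 0.728 | 0.117 | 0.895 | 0.588 |
| 20% PCT only | 0.861 | 0.726 | 0.135 | 0.908 | 0.577 |

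Gaps are taken before rounding; subtracting the rounded values gives 0.079 for 10% each and 0.023 for 20% CRP only. The gap narrows if CRP is copied, alone or equally with PCT, and widens if only PCT is copied.

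**The case against.** The best defence is that the outcome section is the definition and the statistics sentence a loose recap. The defining lists omit CRP and PCT, and *confirmed* infection is microbiological, so neither marker enters it easily. The article also condenses a fuller protocol, where masking of the panel may be set out, so its silence on masking is weak ground by itself.

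Much of this stands. It does not remove the point, because the statistics section makes a positive statement about both standards that conflicts with the definition.

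Four stronger readings are tempting, and the document does not support them:

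- *Both markers are in fact judged against themselves.* The wording permits this but does not show it.
- *The bias raises accuracy for both markers.* With one shared label it need not. If 25% of labels copied CRP only, CRP would rise to 0.793/0.712 (sensitivity/specificity) while PCT would fall to 0.796/0.782.
- *The panel sees PCT in one arm only.* Clinicians have it in the PCT-guided arm, but what a retrospective panel sees is not stated, and "In all patients, both PCT and CRP levels will be available for statistical analysis". The panel might see it in both arms or in neither.
- *Confirmed infection is verified differently by PCT level because fewer blood cultures will be taken.* Background mentions this as a possible saving, not as a trial procedure.

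**Conclusion.** The point holds as a conflict between two sections on the inputs to a primary reference standard. The wider wording admits the tests under evaluation. Followed literally, it permits incorporation bias, mainly in *suspected* infection and much less in *confirmed* infection. The PCT-versus-CRP comparison could be distorted either way: at 10% copying, the planned 0.100 sensitivity gap becomes 0.062, 0.078 or 0.117, depending on what is copied. These sizes rest on assumed copying shares, the article's planning values and independence given true status. They show sensitivity to the problem and do not predict it.

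The secondary measure of antibiotics without suspected infection becomes arm-dependent only if PCT is seen in one arm and not the other. The prescribing outcome and the composite safety endpoint do not depend on the panel's diagnosis and are unaffected.

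**What to change.** - Reconcile the two sections. In the statistics section, end the sentence on how the gold standards are determined with *except PCT and CRP*, and make the outcome definition say the same.
- State that those who set the final diagnosis, and both infection standards, work from files with PCT, CRP, allocated arm and PCT-based treatment advice removed.
- Report accuracy by arm as well as pooled, as a sensitivity check.

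The cost is some redaction of files for a panel that is already planned, and one further table. The panel loses two laboratory values. Masking to arm will be incomplete, because clinical course reflects the treatment given, and the report should say so.
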